## ***12.4 Food Supplements***

Commercially available protein supplements, prebiotic food supplements and maltodextrin (placebo) will be purchased. Indistinguishable sachets will be made up by the company providing the prebiotic food supplement. These can be stored at room temperature. The prebiotic food supplement is called Darmocare Pre®. The composition is Inulin min. 3375mg, fructooligosaccharides (FOS) min. 3488mg per level measuring spoon. Excipients: guaranteed to contain no genetically modified organisms, maize, soy, yeast, gluten, lactose, added saccharose, gelatine, animal substances, preservatives, artificial coloring, flavoring and aromatic substances. Darmocare Pre® has previously been used in studies in older adults, with reported benefits on grip strength and frailty index versus placebo.

Participants can continue their normal diet otherwise. Participants will take their supplement daily mixed in a glass of water or other drink, at the same time of day each day for a 12-week period. All participants will be asked to bring back any remaining sachets at the end of the trial period to help us ascertain compliance.

## ***12.5 End of Study Definition***

Data collection complete and database lock.

## ***12.6 Follow up Procedures***

No follow up procedures will be required for this study as the participants included in the study are healthy volunteers.

# **13 Laboratories**

## ***13.1 Sample Collection/Labelling/Logging***

All sample kits provided, and participant data will be pseudo-anonymised with a unique identifier, the samples may be barcoded to link with participants unique ID. The principal investigator will ensure that all data collected in the study, are recorded in a timely manner according to any instructions provided and the subject numbering process will commence at the point of informed consent. All sample collection kits provided to the participants will contain detailed instruction on storage conditions to ensure the integrity and viability of samples. Participants will be asked to record the date and time of collection for each sample they collect. The samples sent back to the laboratory will be logged in using the unique barcode and/or unique ID. A complete chain-of-custody will be maintained for all samples throughout, from point of acquisition, storage and all uses, including disposal where relevant.

## ***13.2 Sample Analysis Procedures***

Serum will be generated from the whole blood for metabolomics profiling.

Microbiome analysis: Faecal samples will be collected using a sample collection kit provided to the participants. 16s analysis sequencing, and shotgun metagenomics where possible, will be carried out at a reputable institution with a track record of such analyses as a service.

Microbiome markers: Stool samples collected and frozen will be assessed in greater detail for markers of microbiome function. Any remaining sample will be stored at the DTR for potential use in future analysis, such as to allow bridging to other new or improved technologies. The biological (faecal, urine, blood and saliva) samples will be stored at -80C upon receipt and subsequently used for microbiome and metabolomics analysis. These assays will be undertaken by the study investigators or designated collaborators either within or outside of the UK, provided the appropriate Material Transfer Agreements are in place.

### ***13.3 Sample Storage Procedures***

All samples collected will be stored at the Department of Twin Research laboratory at King's College London. Faecal, blood, saliva and urine samples will be stored at -80oC in separate locked, alarmed freezers with CO2 back up and 24/7 on call support. Once all collected, blood and stool samples will be sent to Metabolon, an external laboratory which will carry out the metabolite testing. This is the same lab the department has used for such testing in the past.

Biological samples for future research will be retained at by King's College London for an indefinite period. However, should the tissue have no obvious further use it will be destroyed.

The HTA licence details are as follows:

- Licensing Number: 12522
- Licensed Premises: King's College London, St Thomas' Campus, [name]
- Licence Holder: King's College London
- Designated Individual: [name]

### ***13.4 Data Recording/Reporting***

Data entered into the database and on which the analysis will be performed are pseudonymised, using a unique identification number. At the point of publication, the identification numbers are not published.

A web based electronic data capture (EDC) system will be designed, using the InferMed Macro 4 system. The EDC will be created in collaboration with the trial analysts and the CI and maintained by the King's Clinical Trials Unit for the duration of the project. It will be hosted on a dedicated server within KCL.

The CI or delegate will request usernames and passwords from the KCTU. Database access will be strictly restricted through user-specific passwords to the authorised research team members. It is a legal requirement that passwords to the EDC are not shared, and that only those authorised to access the system are allowed to do so. If new staff members join the study, a user-specific username and password must be requested via the CI or delegate (e.g. Trial Manager) from the KCTU team and a request for access to be revoked must be requested when staff members leave the project. Study site

staff experiencing issues with system access or functionality should contact the CI or delegate (e.g. Trial Manager) in the first instance.

Participant initials and date of birth will be entered on the EDC, NHS number, email addressed, participant names and addresses, and full postcodes will not be entered into the EDC. No data will be entered onto the EDC system unless a participant has signed a consent form to participate in the trial. Source data will be entered by recruiting site staff, typically within 5 days of data collection by authorised staff onto the EDC by going to [www.ctu.co.uk](http://www.ctu.co.uk) and clicking the link to access the MACRO 4 EDC system. A full audit trail of data entry and any subsequent changes to entered data will be automatically date and time stamped, alongside information about the user making the entry/changes within the system. The CI team will undertake appropriate reviews of the entered data, for the purpose of data cleaning and will request amendments as required.

At the end of the trial, the site PI will review all the data for each participant to verify that all the data are complete and correct. At this point, all data can be formally locked for analysis. Upon request, KCTU will provide a copy of the final exported dataset to the CI in .csv format and the CI will onward distribute as appropriate.

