## ***12.3 Randomisation Procedures***

Participants will undergo computer generated block randomisation in twin pairs by the King's College London Clinical Trials Unit (KCTU). A web-based randomisation system will be designed, using the bespoke KCTU randomisation system. The randomisation system will be created in collaboration with the trial analyst/s and the CI and maintained by the King's Clinical Trials Unit for the duration of the project. It will be hosted on a dedicated server within KCL.

The CI or delegate will request usernames and passwords from the KCTU. System access will be strictly restricted through user-specific passwords to the authorised research team members. It is a legal requirement that passwords to the randomisation system are not shared, and that only those authorised to access the system are allowed to do so. If new staff members join the study, a user-specific username and password must be requested via the CI or delegate (e.g. Trial Manager) from the KCTU team and a request for access to be revoked must be requested when staff members leave the project. Study site staff experiencing issues with system access or functionality should contact the CI or delegate (e.g. Trial Manager) in the first instance.

Participant initials and date of birth will be entered on the randomisation system, NHS number, email addresses, participant names and addresses and full postcodes will not be entered into the randomisation system. No data will be entered onto the randomisation system unless a participant has signed a consent form to participate in the trial. Randomisation will be undertaken by authorised staff onto the randomisation system by going to [www.ctu.co.uk](http://www.ctu.co.uk) and clicking the link to access the randomisation system. A full audit trail of data entry will be automatically date and time stamped, alongside information about the user making the entry within the system.

The CI team will undertake appropriate reviews of the entered data, the purpose of data cleaning. No data can be amended in the system, however CI or delegate (e.g. Trial Manager) may request King's Clinical Trials Unit to add notes against individual subject entries to clarify data entry errors. Upon request, KCTU will provide a copy of the final exported dataset to the CI in .csv format and the CI will onward distribute as appropriate. Researchers and participants will be blinded as to which arm each participant is in.

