### ***Randomisation/Allocation Concealment/Blinding Procedures***

Participants will undergo computer generated block randomisation in twin pairs by the King's College London Clinical Trials Unit (KCTU). They will be randomised as twin pairs, with one twin in each arm. Researchers and participants will be blinded as to which arm each participant is in.

On completion of the data collection, the KCTU will issue a blinded list denoting what arm each participant is in (Arm 1; Arm 2), but without revealing which arm is the intervention and which the placebo, in order to facilitate blinded analysis to be carried out. Full unblinding will not take place until data analysis is complete. Until that point, only the KCTU will have access to the unblinded information.

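### The arm-coded list is released when data collection ends, not after database lock, so data queries, outlier checks and imputation decisions can be made with arm groupings to hand

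*Combined protocol and SAP*

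**What the plan says.** **Release of the list.** SAP 3.2 (Randomisation/Allocation Concealment/Blinding Procedures) states: "On completion of the data collection, the KCTU will issue a blinded list denoting what arm each participant is in". The list shows which participants belong together, "without revealing which arm is the intervention and which the placebo". Full unblinding waits until the analysis is finished.

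**Lock.** Protocol 13.4 (Data Recording/Reporting) describes a final check once the trial is over, in which "the site PI will review all the data for each participant to verify that all the data are complete and correct". It continues: "At this point, all data can be formally locked for analysis". Protocol 12.5 defines the end of study by two items: "Data collection complete and database lock".

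**Amendments to the trial database.** Protocol 13.4 also says: "The CI team will undertake appropriate reviews of the entered data, for the purpose of data cleaning and will request amendments as required". Entries and changes are logged with date, time and user.

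**Other data decisions.** SAP section 7 (Descriptive Statistics) has outliers inspected on plots and checked for entry error, with no timing given. SAP section 7 (Missing baseline covariate data) requires imputation choices to be settled before unblinding.

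**Arm labels.** The null hypothesis in SAP section 6 (Primary Outcome) identifies study arm 1 as prebiotic plus protein and study arm 2 as placebo plus protein.

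**The concern.** A blinded analysis protects the primary comparison fully only if outcome values, and the decisions about which values to query, are settled before anyone can sort participants by arm. The SAP ties release of the groupings to the end of data collection, but the protocol leaves the data open to correction after that. Someone who can see the groupings while cleaning could query values in one arm more closely than in the other, deliberately or not. The primary outcome is a single timed measurement per participant at study end, adjusted for baseline, in a trial of about 35 people per arm, so a few values can carry noticeable weight.

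The coding is meant to limit this. It hides treatment identity but not grouping, and here the SAP itself attaches a treatment to each arm number.

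**Working it through.** The plan gives no figure on this point and no arithmetic applies. The check is a comparison of the order of events in the two documents.

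1. **Trigger for the list.** SAP 3.2 sets it at completion of data collection. Lock is not mentioned.
2. **Position of lock.** Protocol 13.4 allows lock once the site PI has verified every participant's data as complete and correct. Lock cannot precede the end of that review.
3. **Position of the review.** A review confirming that all data are complete cannot finish before collection has finished.
4. **Resulting order.** Collection complete, which triggers the list; then PI review finished; then lock. The list's trigger comes no later than the end of the review, and so before lock. Protocol 12.5 also names collection and lock as separate items.
5. **What stays open in between.** Protocol 13.4 lets the chief investigator's team request amendments and gives no cut-off earlier than lock. Neither document makes the list conditional on lock or bars amendments after it is issued. The length of the interval is not stated.
6. **Outlier checks.** SAP section 7 does not place these before or after the list.
7. **Imputation decisions.** The deadline is unblinding. SAP 3.2 puts full unblinding after the analysis. If that is the event meant, these choices may follow release of the list.
8. **Strength of the code.** SAP section 6 pairs arm 1 with prebiotic and arm 2 with placebo. SAP 3.2 names the codes on the list as Arm 1 and Arm 2 but does not say whether they carry that meaning. If they do, holding the list and the SAP together reveals treatment. Supplementary Table S2 (adverse events) uses the same pairing in the reported results. That is consistent with shared numbering but does not prove it, because labels could have been aligned after unblinding.

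**The case against.** **The order is partly inferred.** SAP 3.2 and protocol 13.4 do not refer to each other. The list exists to support analysis, and the data are to be locked for analysis, so staff could lock first and then issue the list, contradicting only the literal trigger. This stands, and it is why the point concerns what the text permits rather than what was done.

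**The recipient is not named.** Overlap between those who see the list and those who can request amendments is possible but not stated. This also stands.

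**The audit trail is a real safeguard.** Once the date of issue is known, every later change to a chair-rise value can be found and attributed to a user. It does not prevent a change or show whether that user had seen the groupings, but it would be wrong to say it gives no protection.

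**Stronger readings that the documents do not support.**
- A reader might infer from protocol 12.3 that the chief investigator can obtain the uncoded allocation before lock, because it says: "Upon request, KCTU will provide a copy of the final exported dataset to the CI in .csv format and the CI will onward distribute". The same section goes on to say that researchers are blinded to arm, and SAP 3.2 reserves unblinded information to the KCTU until analysis is complete. An uncoded export to researchers is therefore barred. A coded export raises the SAP 3.2 question again and needs no separate remedy.
- A reader might put a false-positive rate on the gap by simulating removal of the slowest arm-1 participants. That models conduct the plan does not allow. The intention-to-treat population keeps all randomised participants; outliers are handled by comparing results with and without them; and one-directional removal presumes that the code is known. Such figures would not measure the gap.

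**Conclusion.** The concern holds as an avoidable weakness in sequencing. As written, arm groupings can be available while outcome values, outlier checks and imputation choices are still open, and the code may be readable from the SAP itself.

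The size of any bias is unquantified. It depends on the length of the interval, who receives the list, whether its numbering matches SAP section 6, and how cleaning was carried out, none of which the documents give. A reader might infer that values were altered or that the primary result is compromised; nothing in the documents shows either. The conclusion rests on a literal reading of the SAP 3.2 trigger and on the absence of any statement tying the list to lock.

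**What to change.** In SAP 3.2, replace the trigger with: *After documented database lock under protocol 13.4, with data queries, outlier checks and imputation decisions completed and recorded.*

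Have the KCTU use neutral codes on the list that do not match the treatment labels in SAP section 6.

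No change to protocol 12.3 is needed.

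The cost is one sentence in the SAP and a choice of codes by the KCTU. Outlier and entry-error checks would be done on the pooled data before release, which is sufficient for finding entry errors. Protocol 13.4 already has the data locked for analysis, so no stage is added, and sample size, alpha and model are unchanged. Where the list has already been issued, its date can be set against the audit trail to see whether any chair-rise value was amended afterwards.

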### ***13.5 Sample Transfer to sites outside the Organisation***

Samples may be shared with third parties (e.g. other laboratories) following agreement with King's College London which will comprise the Chief Investigator, the Principal Investigators, GSTT senior staff, professional researchers and lay persons. Transfer of tissue and data to a third party is subject to a separate Material Transfer Agreement issued by King's College London that holds the custodianship of those samples and data. Any tissue transferred outside King's College London will be used up, returned or destroyed once the specific research is completed.

## **14 Assessment of Safety**

As this study is an intervention study, safety monitoring will focus on unanticipated events involving risks to participants, including unanticipated problems that meet the definition of a serious adverse event.

### ***14.1 Definitions***

**Adverse event (AE):** any untoward medical occurrence in a patient or study subject reported to the study team during in person and telephone visits.

**Serious adverse event (SAE):** any untoward and unexpected medical occurrence or event that;

1. Result in death
2. Is life threatening
3. Requires hospitalisation or prolongation of existing in-patient hospitalisation
4. Results in persistent or significant disability or incapacity

Medical judgement will be exercised in deciding whether an AE is serious. Important AEs that are not immediately life-threatening or do not result in death or hospitalisation but may jeopardise the subject or may require intervention to prevent one of the other outcomes listed in the definition above will also be considered serious.

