We have selected an older study population who have a lower than recommended protein intake, and who are weaker, with below average diversity of their gut microbiome. This population represents those who stand to benefit most from a dietary intervention strategy such as the protein plus prebiotic food supplement we are testing in this trial.

In light of the COVID-19 global pandemic and the resulting restrictions on travel, this protocol has been adapted such that all 'visits' will be carried out online, via video teleconferencing software. Participants will take part from home, with the study visits taking place over video teleconferencing. The landscape of research will change drastically in the post COVID-19 era and research carried out remotely, utilising technology and innovative techniques, will become both more common and necessary. A subset of the study population will be invited to the department for repeat physical measures for validation purposes, which will be optional to them.

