## **Stage 3: Dietary intervention**

Control and treatment arms: All participants will be provided with a sachet of powdered food supplement to be taken daily with a glass of water or other drink (hot or cold). All sachets will contain leucine-rich protein supplement.

Sachets for participants in the placebo arm will also contain 20 g of maltodextrin powder (placebo). Sachets for participants in the intervention arm will contain prebiotic food supplement. All participants will be asked to take 1 sachet daily, for a period of 12 weeks. These supplement sachets in each arm will be indistinguishable.

Regular contact will be made with participants by phone/email to encourage compliance and assess for any adverse effects. All participants will be encouraged to engage in regular resistance exercise at least twice per week throughout the intervention and will be provided with written advice on this at the beginning of the study.

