#### **Stage 4: Follow up/end of study measures (visit 2)**

At the end of 12 weeks, participants will be asked to collect stool and urine samples again using the sample collection kits that will be provided to them in their postal pack. Capillary blood, and saliva samples will be collected by the participant, with guidance from a trained researcher, while on the video call. Measurements, and SPPB assessment will be repeated. In advance of the final visit, participants will be asked to complete another 3-day food diary, cognitive test, and to fill in another questionnaire, both of which will be provided in the postal pack, or online.

If participants need more flexibility on the date of their final visit, more sachets can be posted to them to continue the intervention until their final virtual visit, to a maximum of one month's additional intervention time.

**Primary outcome:** chair rise time

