## 10.2 Flowchart

| Stage                                               | 1           | 2                       | 3                            | 4        | 5        | 6              | 7                          |
|-----------------------------------------------------|-------------|-------------------------|------------------------------|----------|----------|----------------|----------------------------|
| Assessment                                          | Eligibility | Pre-baseline video call | Baseline video call (week 1) | Week 3-5 | Week 7-9 | Pre-final call | Final video call (week 12) |
| Inclusion/Exclusion Criteria checks                 | X           |                         |                              |          |          |                |                            |
| Participant information and informed consent        | X           |                         | X                            |          |          |                |                            |
| Randomisation                                       |             |                         | X                            |          |          |                |                            |
| Postal box sent out                                 |             | X                       |                              |          |          |                |                            |
| 3-day food diary (post/online)                      |             | X                       |                              |          |          | X              |                            |
| Questionnaire (post/online)                         |             | X                       |                              |          |          | X              |                            |
| CANTAB cognitive test (online)                      |             | X                       |                              |          |          | X              |                            |
| Provide supplements (post)                          |             |                         | X                            |          |          |                |                            |
| Faecal sample (post)                                |             |                         | X                            |          |          | X              |                            |

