| Capillary blood sample (post)                       |             |                         | X                            |          |          |                | X                          |
| Urine sample (post)                                 |             |                         | X                            |          |          | X              |                            |
| Saliva sample (post)                                |             |                         | X                            |          |          |                | X                          |
| Short Physical Performance Battery                  |             |                         | X                            |          |          |                | X                          |
| Weight (kg) – if scales available                   |             |                         | X                            |          |          |                | X                          |
| Height (cm)                                         |             |                         | X                            |          |          |                | X                          |
| Telephone calls to check compliance/adverse effects |             |                         |                              | X        | X        |                |                            |

|                                                         |  |  |  |  |  |  |   |
|---------------------------------------------------------|--|--|--|--|--|--|---|
| Participants to count
leftover supplement
sachets |  |  |  |  |  |  | X |
|---------------------------------------------------------|--|--|--|--|--|--|---|

[figure not shown]

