## **15 Compliance and withdrawal**

### ***15.1 Subject compliance***

Regular monitoring of compliance will be achieved by regular contact with the participants either via email, text messaging, or telephone. Compliance will be judged by completion of the end of study questionnaires and by the remaining number of sachets at the end of the study. Twin pairs will be advised not to share each other's supplements.

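### Non-serious adverse events late in the intervention may be under-recorded: the last scheduled check is at week 7-9, and the AE definition does not fit the trial's video and email contacts

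*Combined protocol and SAP*

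**What the plan says.** **Definition.** Protocol 14.1 counts as an AE "any untoward medical occurrence in a patient or study subject reported to the study team during in person and telephone visits". The serious adverse event (SAE) definition in the same section, and the SAE reporting rules that follow, name no contact mode.

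**Schedule.** The flowchart (protocol 10.2) has one row for adverse effects, "Telephone calls to check compliance/adverse effects". It is marked under weeks 3-5 and weeks 7-9 only. The final video call at week 12 carries the physical tests, weight and height, blood and saliva samples and a count of leftover sachets. Neither the flowchart nor the Stage 4 text of 10.1 lists an AE question there.

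**Exposure.** Stage 3 of 10.1 states "All participants will be asked to take 1 sachet daily, for a period of 12 weeks". Stage 4 lets a participant who needs a later final visit receive more sachets "to continue the intervention until their final virtual visit, to a maximum of" one further month.

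**Contact modes.** Protocol section 8 has participants at home "with the study visits taking place over video teleconferencing". The only in-person visit is the optional validation visit for a subset (10.1, Stage 5). Stage 3 promises regular phone and email contact whose purposes include assessing adverse effects, but sets no dates. Section 15.1 describes "regular contact with the participants either via email, text messaging, or telephone" for monitoring compliance.

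**After the last visit.** Section 12.6 reads: "No follow up procedures will be required for this study as the participants included in the study are healthy volunteers".

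**Use of the data.** SAP 6.3 (Safety Outcomes) codes adverse effects present or absent for each participant and compares arms by a chi-square or Fisher exact test.

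**The concern.** There are two separate weaknesses.

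- **Timing.** The scheduled checks stop well before the sachets do, and the one contact that every completer has at the end lists no AE question.
- **Definition.** The wording of 14.1 suits a trial with clinic visits and phone calls. Read literally, it leaves out both scheduled study visits, which are by video, and the email contact that Stage 3 itself names for adverse effects.

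What is at stake is the tolerability comparison. An event that starts after the week 7-9 call is recorded only if the participant volunteers it or an undated contact happens to elicit it. Different staff may also treat an event mentioned on a video call or by email differently, because the protocol gives two answers. For an event still present at the final call, 12.6 and the safety section do not say together what happens to its record.

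**Working it through.** The plan states no figure on this point, so there is nothing to reproduce. The check is a comparison of passages and simple arithmetic.

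**1. Does each contact fit the plan's own AE wording?**

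| Contact | Where described | AE purpose stated? | Within 14.1 read literally? |
|---|---|---|---|
| Phone calls, weeks 3-5 and 7-9 | 10.2 | Yes | Yes |
| Regular phone contact, undated | 10.1 Stage 3 | Yes | Yes, at any week |
| Regular email contact, undated | 10.1 Stage 3 | Yes | No |
| Baseline and final video visits | 8; 10.1 Stages 2 and 4; 10.2 | No | No |
| Optional in-person visit, subset | 10.1 Stage 5 | No | Yes |
| Text messages | 15.1 | No, compliance only | No |

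The clear contradiction is the email row: Stage 3 names a route for adverse effects that 14.1 does not count. The video row shows that 14.1 does not match the remote design.

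**2. Exposure after the last scheduled check**

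Gap = end of exposure minus week of last scheduled check. The last check falls between week 7 and week 9 (10.2).

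- Planned end at week 12 (Stage 3): 12 − 9 = 3 weeks and 12 − 7 = 5 weeks. As shares, 3/12 = 25.0% and 5/12 = 41.7%.
- Full extension (Stage 4), with one month assumed to be 4 to 4.35 weeks, so the end is week 16.0 to 16.35:
  - end at 16.0: 7/16 = 43.8% and 9/16 = 56.2%
  - end at 16.35: 7.35/16.35 = 44.9% and 9.35/16.35 = 57.2%
  - overall: about 7 to 9 weeks, 44-57%.

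The second range applies only to someone who uses the whole extension. The documents do not say how many did.

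**3. How sensitive is the planned comparison? (illustration only)**

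Supplementary Table S2 lists 11 events, 9 in arm 1 (prebiotic) and 2 in arm 2 (placebo), with two of the arm 1 events in one participant. Assume no other participant has more than one event and that all 36 per arm (Supplementary Table S6) are in the denominator. Two-sided Fisher tests give:

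| Affected, prebiotic | Affected, placebo | p |
|---|---|---|
| 8/36 | 2/36 | 0.085 |
| 9/36 | 2/36 | 0.046 |
| 8/36 | 3/36 | 0.19 |

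With counts this small, one more affected participant in either arm changes how the result reads. This shows only how fragile the comparison is. It is not evidence that anyone was missed.

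**The case against.** The strongest objection is that Stage 3 already provides regular phone and email contact to assess adverse effects throughout the intervention, with no stop at week 9. A phone report at week 10, 12 or 15 meets 14.1 even on its strictest reading. The row in 10.2 is for telephone calls, so it would naturally be blank under a video-call column, and the final visit is a live conversation with a trained researcher. The in-person wording in 14.1 looks like text left unadapted when the trial moved online, not a rule to discard events. Supplementary Table S7 also shows study-end questions on diarrhoea and constipation over the previous four weeks.

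Much of this stands, and it rules out several stronger readings:

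- A reader might infer that late events are lost by design. The undated Stage 3 contact contradicts that.
- A reader might infer that an event told on the final video call must be coded absent. SAP 6.3 sets no contact mode and no time window and does not cite 14.1.
- A reader might count text messages as an AE route shut out by the definition. Section 15.1 describes them for compliance only.
- A reader might infer that serious events are at risk. The SAE rules carry no contact-mode limit.
- A reader might infer from Table S2 that tolerability was in fact understated. The table gives neither onset dates nor contact mode, so it cannot show loss or its absence.

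The objection does not remove the gap. The Stage 3 promise has no dates, no minimum number of contacts and no standard question, and its email half conflicts with 14.1. The bowel questions cover only some symptoms and are not described as AE collection. Some figures and the full questionnaire are not reproduced in the documents available, so an AE item there cannot be excluded. The flowchart and the Stage 4 text, however, list none.

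**Conclusion.** The point holds as a risk of under-recording non-serious events late in the intervention. No scheduled adverse-effect check covers 25-42% of planned exposure, or 44-57% for a participant on the full one-month extension. These shares measure time without a *scheduled* check, not time without any contact. In addition, 14.1, section 8 and Stage 3 of 10.1 disagree on which contacts can yield an AE and need to be reconciled.

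The conclusion rests on the flowchart being the operative schedule and on a month being 4 to 4.35 weeks. The number of events missed, if any, cannot be estimated from the documents. The change is worth making because it is nearly free and the between-arm comparison rests on few affected participants.

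**What to change.** 1. **Protocol 14.1.** Define an AE as any untoward medical event between the first sachet and the final visit, reported by any route: video, phone, email or questionnaire. This also removes the conflict with section 8 and Stage 3.
2. **Protocol 10.2.** Mark an adverse-effect check at the existing final video call, and add it to the Stage 4 text. Ask it after the physical tests so that it cannot influence chair-rise performance. For anyone on extra sachets, the same check covers the extension weeks.
3. **Protocol 12.6.** Reconcile this section with the safety section so that the two agree on events still ongoing at the final call. How such events are handled is for the investigators to state.

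The cost is wording in two sections and Stage 4, one flowchart mark, a few minutes on a call that already takes place, and slightly more AE recording. No new visit is needed.
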